### 4.2 Analysis of MRI data

Primary imaging analyses will include pre vs. post-LIFUP analysis of reward processing, activation, and connectivity of the caudate and nucleus accumbens as measured with resting state fMRI and task fMRI. Preprocessing of functional MRI data will be done with fMRIprep, Tedana, and XCP-D (Esteban et al., 2020; DuPre et al., 2021; Mehta et al., 2023). Resting state and task fMRI analyses will be conducted using the fMRIB Software Library (FSL) (Woolrich et al., 2001, 2004).

The functional MRI data collected during the Card Guessing Task will be used to assess changes in reward processing across active and sham LIFUP. Reward processing will be assessed by comparing fMRI activation during gain vs. loss trials as well as during gain trials vs. inter-trial intervals. Then, a repeated-measures ANOVA design will be used to assess the effect of time and group on these lower-level contrasts. We hypothesize that participants who received active LIFUP will have higher reward-responsive activity in their respective target regions (i.e., either nucleus accumbens or caudate) compared to those who received sham. This would represent a normalization of activity, as decreased activity has been observed in both regions in response to reward-related tasks (Wang et al., 2021).

Connectivity values between multiple regions of interest will be extracted from the resting state fMRI data in order to investigate changes across LIFUP vs. sham using multi-level modeling. Some particular variables of interest for this analysis due to prior implications for anhedonia in the literature include default mode network average connectivity, left caudate to superior frontal gyrus connectivity, right nucleus accumbens shell to left subgenual anterior cingulate cortex, and right nucleus accumbens core to right precuneus (Dunlop et al., 2019; Liu et al., 2021; Yang et al., 2022).

Additionally, several metabolites measured by MRS will be investigated to elucidate potential changes in reward system neurotransmission across LIFUP vs. sham. MRS data will be processed using Osprey, a software platform developed by the same team that developed the HERMES MRS sequence used for this study (Oeltzschner et al., 2020). Osprey reports metabolite concentrations, relative to water, after correcting for voxel tissue composition and water relaxation rates. GABA+ measurements are additionally corrected to account for differing concentrations in gray and white matter. Primary variables of interest for analysis of the MRS data due to their associations with depression and anhedonia in the literature include concentrations of GABA, Glx (sum of glutamate and glutamine), and glutathione (Sanacora et al., 2012; Luscher and Fuchs, 2015; Tuura et al., 2023). We hypothesize that active LIFUP will result in increases in both GABA and Glx concentrations in the dorsomedial prefrontal cortex, representing a normalization in neurotransmitter levels similar to that observed after successful treatment with other modalities (Sanacora et al., 2003; Chen et al., 2014). Furthermore, we hypothesize that we will observe increased glutathione levels after active LIFUP relative to sham, given our hypothesis of decreased anhedonia and prior findings of lower glutathione in anhedonic participants (Lapidus et al., 2014).

### 4.3 Analysis of digital phenotyping data

Primary variables of interest from the digital phenotyping data include heart rate, heart rate variability, sleep duration, and active energy burned. Multi-level modeling will be utilized to investigate between-group differences in these measures across LIFUP (or sham) stimulation. After analysis of these primary variables, further exploratory analyses will be conducted with a broader set of digital phenotyping variables; selection of these variables will likely be guided by OPTIMA analyses assessing correlations between digital phenotyping measures and anhedonia severity.

### 4.4 Predictive analyses

Two primary sets of predictive analyses will be conducted utilizing a machine learning approach, both aiming to identify predictors of LIFUP response as measured by change in score on the PVSS and PHQ-14. First, in order to maximize power given the relatively small sample size of this study, a smaller subset of potential predictors (~50) will be analyzed. These predictors will be selected based on both the literature and the results of analyses from the OPTIMA study exploring potential MRI, digital phenotyping, and self-report-based predictors of anhedonia severity. Subsequently, an exploratory bottom-up approach will be used to investigate other potential predictors that were not in the initial subset. This analysis will utilize all features across all data modalities in conjunction with ensemble machine learning techniques including dimensionality reduction and automated machine learning.

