#### 2.1.1 Inclusion/exclusion criteria

A complete list of inclusion/exclusion criteria for this study is available in Table 1.

**Table 1 T1:** Inclusion and exclusion criteria.

**Inclusion criteria**	**Exclusion criteria**
Age 18–65	Current tobacco smoker of >11 cigarettes/day or the nicotine equivalent
Fluent in English	Current report of alcohol or substance abuse or dependence
Right-handed	Recent changes in antidepressant dosing or medication (dose and medication need to be stabilized within the last 2 weeks)
Healthy or corrected to healthy vision	Reported diagnosis of schizophrenia or psychotic symptoms
Residing in Los Angeles area for the duration of study	Currently taking benzodiazepines, or taken benzodiazepines in the past 8 weeks
Own functioning iOS smartphone (iPhone 8 or later, iOS 15 or newer) with access to reliable data plan and Wi-Fi	History of medical event(s) or diagnoses likely to result in neurological abnormalities including diagnoses of Alzheimer's, Parkinson's, neurodegenerative disorders, movement disorders, reports of past seizures or stroke, or history of brain tumors or brain surgery.
Able to read and understand a written informed consent form	Medical conditions involving chronic mobility impairment including spinal cord injuries, or severe osteoarthritis of knee or hip
Willing to participate in the study and complete required tasks as outlined in study timeline, including MRI, LIFUP, Apple Watch wear, and surveys	Unwilling or unable to refrain from making significant changes to hairstyle after enrollment and before LIFUP sessions are complete (i.e., full hairstyle to shaved head, significant change in locs, etc.)
Eligible for MRI scanning and neuromodulation	Contraindications for MRI scanning, including pregnancy, metal implants, braces, significant grip impairment and claustrophobia
PVSS < 6.5 at screening and stable for ≥12 weeks, as indicated by average scores across OPTIMA protocol or by self-report for those screened from general population	Any previous treatment with electroconvulsive therapy (ECT) or deep brain stimulation (DBS) due to increased risk of seizure and unclear evidence of how LIFUP will affect individuals who have received these treatments.

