PHQ scores > 10 at screening and stable for ≥12 weeks, as indicated by average scores across OPTIMA protocol or by self-report for those screened from general population	Less than 6 months since any other neuromodulation treatment such as transcranial magnetic stimulation (TMS), Vagal nerve electrostimulation, or transcranial direct current stimulation (TDCS).
If screened from OPTIMA, have completed the majority of OPTIMA assessments	Less than 6 months since prescribed ketamine infusion or other intensive, acute therapy for depressive symptoms.

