## 4 Planned analyses

### 4.1 Analysis of self-report measures

Primary analyses of self-report data will leverage multi-level modeling to assess the time course of response to LIFUP as well as the difference in response between the active and sham LIFUP groups. The active nucleus accumbens and active caudate conditions will be pooled for the primary analyses, with a second analysis being conducted with only the caudate group vs. sham. The primary variables of interest for these models will be total score on the PVSS and PHQ-14, and EMA variables measuring positive and negative affect. As a secondary analysis, we will re-run this multi-level modeling with the inclusion of the total score on the first eight items of the PHQ-9 (such that total score aligns with PHQ-14 total score) administered one day after each LIFUP session.

Additionally, chi-square analyses will be conducted to assess differences in response rate between sham and active LIFUP, where response will be defined as a 25% or greater score reduction on PHQ-14 or score increase on the PVSS between baseline and the Week 3 survey timepoint (i.e., ~1 week post-LIFUP). We hypothesize that active stimulation of either caudate or nucleus accumbens will be associated with a decrease in PHQ-14 score and increase in PVSS score relative to sham stimulation. This hypothesis is supported by literature showing associations between decreased reward sensitivity in anhedonic depression and hypoactivity in the striatal regions that this study aims to excite (Wang et al., 2021). Similarly, we hypothesize that the EMA data will show an increase in positive affect and a decrease in negative affect after active stimulation relative to sham.

For secondary outcome measures with only two timepoints, repeated measures ANOVA will be used to investigate the effect of time (pre vs. post-LIFUP) and group (active caudate vs. active nucleus accumbens vs. sham).

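### Section 4.4 defines LIFUP response as within-person change and names no sham contrast, so predictors of change could be reported as predictors of response to LIFUP

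*Protocol article*

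**What the plan says.** Section 4.4 announces the work as follows: "Two primary sets of predictive analyses will be conducted utilizing a machine learning approach". The aim of both sets is to "identify predictors of LIFUP response as measured by change in score on the PVSS and PHQ-14". In the first set, "a smaller subset of potential predictors (~50) will be analyzed". These candidates come from the literature and from OPTIMA analyses "exploring potential MRI, digital phenotyping, and self-report-based predictors of anhedonia severity". The section does not say whether sham participants enter the models, and it names no arm term and no baseline adjustment.

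The neighbouring sections do name the comparison. Section 4.1 will assess "the difference in response between the active and sham LIFUP groups". Section 4.2 sets LIFUP against sham for the imaging and spectroscopy measures, and Section 4.3 looks at between-group differences in the digital measures. Section 4.1 also gives a within-person meaning to the word: "response will be defined as a 25% or greater score reduction on PHQ-14 or score increase on the PVSS", between baseline and Week 3. There, however, the resulting rates are compared between sham and active.

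Entry depends on the same two constructs, "PVSS < 6.5 at screening" and "PHQ scores > 10 at screening" (Table 1). Each must also have been stable for at least 12 weeks, shown by average OPTIMA scores or, for recruits from the general population, by self-report.

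**The concern.** A participant's change after LIFUP mixes several things: any effect of the stimulation, placebo response, the natural course of the episode, and regression to the mean. Only the comparison with sham separates the first from the rest. A target defined as change alone does not make that separation, under either plain reading of Section 4.4:

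- **Active participants only.** Every prognostic marker of improvement looks like a predictor of LIFUP response.
- **Both arms pooled without an arm term.** The same happens with a larger sample, so prognostic markers are found more often.

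The choice of candidates adds to the risk. Variables picked partly because they track anhedonia severity are likely to be related to baseline score, and baseline score is correlated with change even when treatment does nothing. Validation would not expose the problem, because a prognostic marker really does predict change and would hold up in held-out data. At stake is a list of apparent predictors of benefit that could misdirect participant selection in later trials.

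**Working it through.** The article gives no power, effect size, standard deviation or retest figure, so there is no stated number to reproduce. The check asks how often a variable with no bearing on LIFUP effect would be flagged.

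**Inputs from the article.** At least 40 evaluable participants (Section 2.1); current allocation at equal rates (Section 3.1.1); target and candidate list as in Section 4.4.

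**Assumptions not in the article.** 20 active and 20 sham; no LIFUP effect for anyone; normal scores with equal variance before and after; baseline-to-follow-up correlation ρ of 0.6, 0.7 or 0.8; a two-sided 5% linear test standing in for the machine-learning step; baseline score treated as one of the candidates. Twenty per arm is only approximate, because the earlier three-condition phase allocated two active to one sham.

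**Step 1: correlation of baseline with change, no range restriction.** In SD units, Cov(baseline, change) = ρ − 1 and Var(change) = 2(1 − ρ). Hence

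corr = −(1 − ρ)/√[2(1 − ρ)] = −√[(1 − ρ)/2],

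which is −0.447, −0.387 and −0.316 for ρ = 0.6, 0.7 and 0.8. This needs no selection, only an imperfect retest correlation.

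**Step 2: the same with a restricted baseline range.** If the baseline variance is v after a cut, then

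corr = −(1 − ρ)√v / √[(1 − ρ)²v + 1 − ρ²].

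A cut at the mean gives √v = 0.603. At ρ = 0.7 this is −0.3 × 0.603/√(0.09 × 0.363 + 0.51) = −0.181/0.737 = −0.245. A cut at +1 SD gives √v = 0.446 and −0.184. Restriction weakens the correlation but does not remove it.

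**Step 3: how often baseline severity is flagged (simulation; ranges run from ρ = 0.8 to ρ = 0.6).**

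| Baseline range | Active only, n = 20 | Arms pooled, n = 40 | Predictor-by-arm test |
|---|---|---|---|
| Unrestricted | about 28–53% | about 52–84% | about 5% |
| Cut at the mean | about 14–25% | about 24–46% | about 5% |
| Cut at +1 SD | about 10–15% | about 15–27% | about 5% |

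Simulation error is a percentage point or two.

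**Step 4: a purely prognostic marker.** For a marker correlated 0.3 to 0.5 with change equally in both arms, the flag rate is about 25–64% in active-only analyses and 47–94% in pooled ones. The predictor-by-arm test again stays at about 5%.

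**Step 5: the price of the contrast.** For a true modifier correlated 0.5 with change in the active arm and 0 in sham, the interaction test has about 34% power, against about 65% for an active-only test.

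**The case against.** The strongest reply is that Section 4.4 is silent rather than wrong. A reader might infer that it commits to raw change, to active participants only, or to no baseline adjustment. It states none of these. A change outcome is compatible with an arm term, a baseline covariate and sham participants in the model, and a condensed article may leave those to an analysis plan that is not shown. This stands as a limit on the wording: the plan permits the error but does not prescribe it. It does not dispose of the point, because the target itself is fixed in the text and the equally condensed sections around it do name the contrast.

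Three further replies have force.

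- **Selection is not the cause.** A reader might infer that the entry cut-offs create the correlation between baseline and change. They do not. Selection shifts the mean change, while restricting the range weakens the correlation. The unrestricted rates are therefore an upper illustration.
- **Stability.** The 12-week criterion reduces regression to the mean, most credibly where OPTIMA scores are averaged. Self-reported stability does less, and neither form addresses prognosis or placebo response.
- **Method.** The plan is machine learning, not one test per variable, and does not say that baseline score is a candidate. The rates show the direction and rough size of the problem; they are not predictions for the planned models.

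A reader might also be tempted to count chance findings at p < 0.05 among the roughly 50 candidates. The article proposes no such screening, and it uses the reduced set to narrow a wider search in a sample it acknowledges is small. That argument is not made here.

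**Conclusion.** The point holds in a limited form. As worded, Section 4.4 attaches the label LIFUP response to within-person change and omits the sham contrast that its sibling sections name. Followed on either plain reading, it cannot tell a modifier of LIFUP effect from a prognostic marker. Under the stated assumptions, false labelling of baseline severity ranges from about 10% to 53% with active participants only and from about 15% to 84% with arms pooled, against about 5% with a predictor-by-arm test. The spread reflects the unknown retest correlation and how far entry criteria narrow the baseline range. The entry cut applies at screening rather than at the baseline measurement itself, so the truth may lie between the restricted and unrestricted rows.

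It would go too far to infer that the trial's efficacy conclusion is at risk. The sets are primary among the predictive analyses, and the randomised comparison in Section 4.1 names sham and is untouched. The correction is worth making because it concerns what the results may be called, and the sham data needed for it are collected anyway.

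**What to change.** Amend Section 4.4 as follows:

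1. Fit the predictive models in both arms, with the follow-up PVSS or PHQ-14 score as outcome and the baseline score as covariate.
2. Call a variable a predictor of LIFUP response only on its predictor-by-arm contribution.
3. Report main effects as prognostic predictors of change.
4. Label the results hypothesis-generating, and state that power for interactions is low at about 40 participants.

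If the sponsor prefers to keep change as the target without a sham contrast, the outputs should be renamed predictors of change.

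The cost is wording and some computing, with no new data. The real downside is precision: in the illustration, power falls from about 65% to about 34% for a strong true modifier, so fewer predictors will be claimed. The higher figure belongs to a test that cannot distinguish a modifier from a prognostic marker, so it is not a reason to keep the present target.

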### 4.5 *Post-hoc* exploratory analyses

Given the breadth of data collected through this protocol, a wide variety of both hypothesis-based and exploratory analyses will be possible that have not yet been developed.

## 5 Discussion

Direct stimulation of reward-related subcortical regions is an approach that has proven highly effective in individuals with major depressive disorder (Figee et al., 2022). However, due to the invasiveness and risks associated with surgical DBS, the studies conducted to date have been primarily open-label, small-sample studies of participants with severe, highly treatment-resistant depression. The investigation of caudate and nucleus accumbens stimulation with LIFUP in this protocol will therefore help to elucidate the potential efficacy of this intervention in individuals with a wider range of depression severity and treatment resistance than those who have been studied previously. Furthermore, despite the literature implicating the caudate in the mechanism of anhedonic depression, direct stimulation of the caudate has been minimally investigated as a potential treatment for depressive symptoms. If caudate stimulation is found to be effective through this protocol, it could highlight a new potential target for both invasive and non-invasive deep brain stimulation for individuals with depressive disorders.

This study is also one of the first studies to investigate the effects of multiple sessions of deep brain LIFUP on depressive and anhedonic symptoms; previous multi-session LIFUP studies in clinical populations have found significant impacts on anxiety symptoms (Mahdavi et al., 2023), autism spectrum disorder symptoms (Cheung et al., 2023), and worry symptoms (Reznik et al., 2020). Furthermore, a single, 40-min session of LIFUP to the subcallosal cingulate cortex was recently found to reduce depressive symptoms in individuals with treatment resistant depression (Riis et al., 2024a,b). However, none of these previous studies included longitudinal neuroimaging measures or continuous physiological monitoring. As a result, this study is a critical step forward in the investigation of the potential neurological and physiological effects of multi-session deep brain LIFUP. This is especially important given that most other non-invasive brain stimulation techniques used in psychiatric applications, such as transcranial magnetic stimulation (TMS) and transcranial direct current stimulation (TDCS) require multiple sessions for optimal treatment response (Li et al., 2022; Hutton et al., 2023). While this study still does not reach the 10+ sessions typically used in TMS and TDCS applications, a demonstration of the feasibility and safety of multi-session LIFUP through this protocol would provide support for the investigation of more intensive LIFUP protocols in future studies.

A notable limitation of this study protocol is the timeline variability across participants. The time course of LIFUP effects after multiple consecutive sessions has not yet been investigated and is therefore unknown. Thus, while the 3–14 day window between the last LIFUP session and the post-LIFUP MRI is necessary for the logistical feasibility of the study, there is a chance that the effects observed in the neuroimaging data for each participant may be strongly impacted or even rendered undetectable by the relative timing of the post-LIFUP MRI. This is a critical confound that will need to be controlled for in analyses; however, this range of timepoints may also facilitate investigation of the time course of post-LIFUP changes in neurological function.

Due to budget changes partway through the study, it was necessary to remove the nucleus accumbens condition from this study. As a result, the nucleus accumbens group sample size is markedly smaller than initially intended, limiting the power of subsequent analyses for this target. However, this reduced sample (six active participants) still represents the largest study to date of nucleus accumbens LIFUP, and the only one in depressed participants (Mahoney et al., 2023; Peng et al., 2024). Furthermore, the previous studies found significant effects even with smaller samples, suggesting that the data collected for this condition may still be sufficient to detect potential effects (Mahoney et al., 2023; Peng et al., 2024). Another sample-related limitation lies in the nature of study participation; depressed participants who are willing and able to participate in a research study requiring multiple in-person visits and an array of remote tasks may have different characteristics and symptom profiles than the broader population of individuals with anhedonic depression, limiting the generalizability of our data.

In conclusion, this double-blinded, sham-controlled study aims to investigate the effects of non-invasive subcortical brain stimulation with LIFUP to the left caudate head and right nucleus accumbens in individuals with anhedonic depression. Through the extensive MRI, self-report, and digital phenotyping data being collected through this protocol, it will be possible to investigate a wide variety of potential effects of LIFUP, as well as an array of potential predictors of response. If LIFUP is found to effectively modulate brain activity and levels of anhedonia, it could open up a path toward a new, critically-needed alternative to surgical deep brain stimulation in patients with treatment-resistant depression.

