## 2 Materials and methods

### 2.1 Subject population

This protocol will enroll up to 100 right-handed adult participants with high anhedonia and moderate or high depression, with the goal of achieving an evaluable sample of at least 40 participants. For the purposes of this protocol, evaluable participants are defined as those who complete all three LIFUP sessions, both MRI scans, and at least one outcome measure after completing LIFUP.

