### 3.1 Intervention protocol

#### 3.1.1 Condition assignment

Following screening and enrollment, participants are block-randomized to one of two conditions at equal rates: (1) active stimulation to the left caudate or (2) sham stimulation to the left caudate. A previous version of this protocol block-randomized participants into three conditions at equal rates: (1) active stimulation to the left caudate head, (2) active stimulation to the right nucleus accumbens, or (3) sham (assigned to left caudate or right nucleus accumbens to maintain concealment of conditions); however, due to budget changes, randomization to the “active stimulation to the right nucleus accumbens” condition was removed; a total of six participants were assigned to the active nucleus accumbens condition prior to its removal.

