The initial design of this study utilized three gel pads, one of which was sham. Participants in both the nucleus accumbens and caudate group were randomized to gel pads A, B, and C at equal rates, such that 1/3 of participants would receive active caudate, 1/3 would receive active nucleus accumbens, 1/6 would receive sham caudate, and 1/6 would receive sham nucleus accumbens. When it was determined due to funding changes that the study design should be reduced to two conditions, one individual on the team was unblinded by steering committee consensus. This individual then performed analyses on the imaging data from the Card Guessing Task to determine changes in reward attainment and anticipation across LIFUP in each group in order to guide a data-informed decision on which condition to keep in the study. Results of the analyses were then presented to the investigative team, keeping conditions concealed. Based on these results, investigators chose a condition to keep in the revised protocol, and an alternate condition was designated to keep in the case that the primary choice was sham. Investigators were informed that the nucleus accumbens target would be removed, but were not informed which group in the presented analyses was the active caudate group. The only individuals who were knowledgeable about condition assignment were the individual who performed the analysis and the research program manager who supervised the staff performing LIFUP. Conditions remained concealed to all other members of the research team. A total of six participants received active nucleus accumbens LIFUP prior to the removal of this condition.

To maximize the integrity of blinding, outcome assessors refrain from making any guesses regarding active/sham conditions. In the case where a participant guesses their condition based on how they feel during sessions, staff listen to their thoughts but refrain from discussion, and no records of these guesses are kept.

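### Significance in smaller earlier studies does not show that six accumbens participants may be enough: only differences of about 1.2 to 1.5 SD are detectable, and the two-timepoint secondary analysis should name caudate versus sham as its test

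*Protocol article*

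**What the plan says.** Section 3.1.1 of the protocol article records that "a total of six participants were assigned to the active nucleus accumbens condition prior to its removal", and section 3.1.3 gives the same count for those who received it: "A total of six participants received active nucleus accumbens LIFUP prior to the removal of this condition". The arm is closed, so six is its maximum.

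Section 5 (Discussion) acknowledges that the small group limits power for this target. It then adds that "this reduced sample (six active participants) still represents the largest study to date of nucleus accumbens LIFUP" and, because smaller studies had found significant effects, that "the data collected for this condition may still be sufficient to detect potential effects". No effect size, SD, alpha or power accompanies this.

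Section 4.1 treats the arm in two ways:
- **Primary self-report models:** the two active targets are pooled against sham, and a second analysis compares caudate with sham.
- **Secondary outcomes with two timepoints:** a repeated-measures ANOVA uses time and "group (active caudate vs. active nucleus accumbens vs. sham" as its factors. No caudate-versus-sham analysis is named for these outcomes.

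Section 4.2 also states an imaging hypothesis against sham for each target region, accumbens included.

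**The concern.** The reassurance rests on a faulty step. A significant result in a very small study does not show that a study of that size is adequately powered. Such results tend to be the overestimates that happened to cross the threshold. The Discussion also says that no earlier accumbens study was in depressed participants, so their effects cannot simply be carried over to this population.

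The sentence bears on planned inference, since accumbens is a separate group level in section 4.1 and has its own imaging hypothesis in section 4.2. A reader who accepts it could take a null accumbens result as evidence against the target, or take a significant one at face value when its size is likely to be inflated.

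The second issue is which test answers the caudate question for the two-timepoint secondary outcomes. Section 4.1 does not say whether it is the overall three-group effect or a contrast, and under plausible conditions the two differ in power.

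**Working it through.** The plan gives no power figure to reproduce. Effects are in SDs of the analysed variable. For a two-timepoint ANOVA, the group-by-time comparison of two groups is a two-sample test on change scores.

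**Inputs**
- Active accumbens: 6 (sections 3.1.1, 3.1.3 and 5).
- Total: up to 100 enrolled, "with the goal of achieving an evaluable sample of at least 40 participants" (section 2.1).
- Allocation: now "participants are block-randomized to one of two conditions at equal rates" (section 3.1.1); originally "1/3 of participants would receive active caudate, 1/3 would receive active nucleus accumbens, 1/6 would receive sham caudate", with the remaining sixth to sham accumbens (section 3.1.3).
- Sham size is not stated, so it is an assumption: 40/3 ≈ 13; (40 − 6)/2 = 17; 40/2 = 20; (100 − 6)/2 = 47.
- Alpha 5% two-sided and 80% power are assumptions.

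**Step 1: what six participants can detect**

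Power comes from the noncentral t with df = 6 + n − 2 and noncentrality d × √(6n/(6 + n)), where n is the sham size. The 95% CI half-width is t(0.975, df) × √(1/6 + 1/n).

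| Sham n | Detectable d, 80% power | Power at d = 0.5 | Power at d = 0.8 | CI half-width (SD) |
|---|---|---|---|---|
| 13 | 1.47 | 16% | 33% | 1.04 |
| 17 | 1.40 | 17% | 36% | 0.99 |
| 20 | 1.36 | 18% | 38% | 0.96 |
| 47 | 1.24 | 20% | 44% | 0.87 |

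For n = 17, √(6 × 17/23) = 2.106. At d = 1.40 the noncentrality is 2.95 on 21 df, with critical value 2.080, giving 80% power.

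Recruiting more sham participants cannot solve this. By the normal approximation, as n grows without limit the detectable d tends to (1.96 + 0.84)/√6 ≈ 1.14. Against only about six concurrent sham participants (an assumption), it is 1.80.

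In baseline SD units, change scores with pre-post correlation ρ multiply 1.40 by √(2(1 − ρ)). This gives 1.66, 1.40, 1.08 and 0.89 at assumed ρ of 0.3, 0.5, 0.7 and 0.8.

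**Step 2: how far a significant result would overstate**

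Simulating 6 versus 17, the mean absolute difference among significant results is about 2.3 times the truth when d = 0.5, and about 1.6 times when d = 0.8.

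**Step 3: the three-level factor**

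Assume 40 evaluable participants split as 17 caudate, 17 sham and 6 accumbens, with a true caudate effect of 0.8 and sham 0. The omnibus test is F on (2, 37) df with noncentrality λ = Σ nᵢ(μᵢ − μ̄)².

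| Accumbens effect | λ | Omnibus power |
|---|---|---|
| 0 or 0.8 | 6.26 | 57% |
| 0.4 | 5.44 | 50.5% |
| 1.0 | 7.28 | 64% |
| 1.2 | 8.70 | 72% |

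The direct caudate-versus-sham comparison has noncentrality 0.8 × √(17 × 17/34) = 2.33. Power is 61.9% as a two-group test (32 df) and 62.2% as a contrast inside the three-level model (37 df).

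**The case against.** The strongest reply is that the article already discloses the problem. The sentence before the reassurance concedes limited power, and the reassurance itself is hedged. This stands: the article is not silent on power and does not claim adequacy outright. What remains wrong is that the concession is then offset by an argument that cannot support it.

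A reader might infer that keeping accumbens in the ANOVA damages the caudate-versus-sham comparison. The documents and the arithmetic do not support that. Within the model the contrast keeps its power (62.2% against 61.9%). Only a 2-df omnibus test loses power, and only for some accumbens effects; at 1.0 or 1.2 SD it gains. Section 4.1 does not say that inference rests on the omnibus test, and handling of contrasts may be set out in an analysis plan that is not shown.

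A reader might also infer that the main analyses are compromised. They are not on this account: the primary self-report models pool the two active targets, and a caudate-versus-sham analysis is added for those outcomes.

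Nor do the documents require that the arm be removed from the model or never tested. Keeping a randomised arm in the model and reporting estimates with intervals is legitimate. The misreadings described above are risks, and the stated power caveat partly guards against them.

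Finally, the sham size, alpha and 17/17/6 split are assumptions. The exact figures depend on them. The finding of low power does not, since it holds at every sham size tried.

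**Conclusion.** The concern holds in a limited form. The inference from earlier significant results to possible sufficiency is invalid. With six active participants, 80% power requires a true difference of about 1.2 to 1.5 SD for 13 to 47 sham participants, and power at d = 0.8 is about 33% to 44%. If any of the six is not evaluable as section 2.1 defines it, the position is worse.

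The point on the three-level factor is conditional. If the omnibus group effect is the test, power for a caudate effect of 0.8 SD is about 51% to 57% when the accumbens effect lies between 0 and 0.8, against 62% for the direct contrast. The contrast itself is unharmed.

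The point concerns one Discussion sentence, the status of accumbens-specific results, and the unnamed test for two-timepoint secondary outcomes. It does not reach the primary self-report analysis.

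**What to change.** - **Section 5:** replace the sufficiency sentence with the detectable effect, about 1.2 to 1.5 SD at 80% power and two-sided 5%, with the sham size assumed. Keep the existing concession on power.
- **Accumbens-specific results, including the imaging hypothesis in section 4.2:** label them descriptive and report estimates with confidence intervals.
- **Section 4.1, secondary outcomes with two timepoints:** name the caudate-versus-sham time-by-group contrast as the test of interest. It may be fitted within the three-level model or as a two-group model. This matches the caudate-versus-sham analysis already planned for the primary self-report outcomes.

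The cost is a change of wording and one line of model specification, with no new data. The downside is that no confirmatory claim can be made for accumbens.
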